### Outcomes

Outcomes will be assessed by independent KM doctors who will be blinded to the randomization. The outcome assessors will be trained before the study begins and will follow the SOP of this trial.

### Primary outcome

The primary outcomes are: (1) NRS of fatigue, (2) brief fatigue inventory (BFI), (3) fatigue severity scale (FSS), and (4) evaluation of adverse events (AEs). Outcome measures will be collected at baseline and at weeks 5 and 13.

The NRS for fatigue is a self-assessment of the average intensity of fatigue symptoms during the past week. Each participant will score on a 0–10 scale.

The BFI consists of nine items using numeric scales from 0 to 10 to assess the severity and interruption of daily life during the previous 24 h. Three items evaluate the degree of current fatigue from the usual to the worst level, while the other six items assess disturbances in daily activity. The total BFI score is calculated as the mean of the nine-item scores. A previously validated Korean version of the BFI will be used (25).

The FSS contains nine statements that evaluate the severity of fatigue symptoms using a 7-point Likert self-rating scale. The score will be calculated as the sum of the nine item scores, and the cut-off value is thirty-six. A previously validated Korean version of the FSS will be used (26).

AEs related to acupuncture treatment include needle-site pain, skin bruising, bleeding, dizziness, anxiety, and infection. All unexpected and unintended responses related to acupuncture will be recorded by the investigators after each treatment session. A causal relationship between treatment and AEs will be categorized using a 1–6 scale (1 = definitely related; 2 = probably related; 3 = possibly related; 4 = probably not related; 5 = definitely not related; 6 = unknown), and the severity of AEs will be scored using Spilker’s classification (1 = mild; 2 = moderate; 3 = severe).

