**Methods:**

Thirty patients will be recruited and randomly assigned to either the acupuncture or sham acupuncture treatment groups. Treatment will be conducted thrice a week for both groups during 4 weeks. The primary outcome will be the efficacy and safety of acupuncture, including numeric rating scale (NRS), brief fatigue inventory (BFI), fatigue severity scale (FSS), and adverse event evaluation. Secondary outcomes will be evaluation of improvement in the comorbid symptoms of fatigue and feasibility variables. Outcome variables will be assessed before treatment, 4 weeks after treatment, and 8 weeks after treatment completion.

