## Study objectives

The aims of this pilot RCT will be as follows: (1) to test the efficacy and safety of acupuncture treatment for patients experiencing persistent fatigue after recovery from COVID-19 and (2) to explore the feasibility of future full-scale RCT.

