### Participants

A formal sample size calculation was not performed because this was designed as a pilot study to calculate the appropriate sample size for subsequent RCTs. Our study will recruit 30 patients, based on previous studies that recommended the minimum number of people necessary for preliminary research in the field of life sciences to be 10 to 35, considering a 20% drop-out (16–18).

Participants who have the following conditions will be included: (1) aged 20 to 65 years; (2) diagnosed with COVID-19 and quarantined (and cured) at least 1 month ago; (3) experiencing newly developed fatigue that has persisted for more than 4 weeks after being cured of COVID-19, and whose symptom intensity is 4 or higher on the 0–10 numeric rating scale (NRS); and (4) voluntarily agreeing to participate in the study through a written consent form after listening to the purpose and characteristics of this clinical study.

Participants who have one or more of the following conditions will be excluded: (1) having history of diseases (cancer, anemia, hypothyroidism or psychiatric disease such as depression) or surgical operation that can cause fatigue symptom before the infection of COVID-19; (2) having fear of acupuncture treatment; (3) pregnant, breast feeding or expecting a pregnancy during the study period; (4) judged to find it difficult to comply with this treatment protocol (e.g., visiting the hospital, or filling in a questionnaire); (5) participating in another clinical study; (6) with other factors deeming them inadequate for participation in the view of research investigators.

Eligible patients will be informed of the aims and potential benefits, risks, alternatives, and responsibilities of the study by a Korean Medicine (KM) doctor throughout the consent process and written consent will be obtained. The patients’ information will remain confidential, and they will have the right to withdraw without prejudice at any time.

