### Statistical analysis

Statistical analyses will be performed on both an intention-to-treat (ITT) basis and per-protocol (PP) population (95% confidence interval [CI]) using the SAS package program (Version 9.4; SAS Institute Inc., United States). Missing data will be replaced according to the last observation carried forward (LOCF) method. Baseline characteristics will be shown as mean ± standard deviation (SD) for continuous data and n (%) for categorical data. To analyze the baseline characteristics, we will conduct between-group comparisons at baseline using two-sample *t*-test or Wilcoxon rank sum test for continuous data and chi-squared test or Fisher’s exact test for categorical data with *p* < 0.05, as statistically significant, to determine whether the data are normally distributed.

For primary and secondary outcome measures, the mean difference from the baseline values to the end of treatment in each group will be compared using a two-sample *t*-test or Wilcoxon rank-sum test. If we needed to compare repeated measures, we would implement the repeated measures ANOVA. If any imbalances in baseline characteristics between groups were encountered, we will conduct analysis of covariance (ANCOVA) using these variables as covariates and the randomized group as a fixed factor. We might conduct subgroup analysis according to the baseline demographics, such as analysis on symptom duration over or under than 3-month period. In addition, to compare pre and post treatment assessment, we would use paired *t*-test, after evaluating the normality of the data. The safety and feasibility variables are descriptively presented with detailed explanations. Blinding assessment will be analyzed using Bang’s blinding index (29).

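### Three fatigue scales are all primary with no lead scale or success rule; if any one may carry the efficacy claim, the end-of-treatment false-positive chance is about 8.5% to 14%, not 5%

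*Protocol article*

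**What the plan says.** The Primary outcome section of the protocol article reads: "The primary outcomes are: (1) NRS of fatigue, (2) brief fatigue inventory (BFI), (3) fatigue severity scale (FSS"), and lists adverse events as a fourth primary item. The Methods paragraph of the Abstract bundles the same items: "The primary outcome will be the efficacy and safety of acupuncture". Neither place ranks the scales or says what pattern of results would count as success.

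The first aim under Study objectives is "to test the efficacy and safety of acupuncture treatment for patients experiencing persistent fatigue after recovery from COVID-19". The Discussion adds that the design meets the principle of adequate power, without giving a figure.

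On timing, the Primary outcome section says "Outcome measures will be collected at baseline and at weeks 5 and 13". The Statistical analysis section fixes the between-group comparison at one point: "the mean difference from the baseline values to the end of treatment in each group will be compared using a two-sample" t-test or a Wilcoxon rank-sum test. Repeated-measures ANOVA is to be used if repeated measures need comparing, with no criterion for that need. Analyses are planned in both the intention-to-treat (ITT) and per-protocol (PP) sets. Within-arm tests are also planned: "In addition, to compare pre and post treatment assessment, we would use paired" t-tests. No multiplicity adjustment is mentioned. The 0.05 level appears only in the sentence on baseline comparisons.

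**The concern.** NRS, BFI and FSS all measure the severity or impact of fatigue. With all three primary and unranked, a reader cannot tell in advance which result would mean that acupuncture worked. Whichever scale turns out favourable can be reported as the primary result without departing from the protocol.

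Two things are at stake. The first is the false-positive risk attached to a stated aim of testing efficacy. The second is the next trial: the limitations paragraph of the Discussion says these data will feed its sample size calculation. If the most favourable of three noisy estimates is carried forward, that trial will be planned on an optimistic effect.

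**Working it through.** **The plan's own figure.** The article states no family-wise error rate, effect size, SD or power figure, so there is no error rate to reproduce. The only design number is 30 patients, taken from a rule of thumb (Participants).

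**Inputs.**
- Efficacy scales named primary: 3 (Primary outcome). Adverse events are to be reported descriptively, so they add no test.
- Between-group comparisons per scale: 1, change from baseline to end of treatment (Statistical analysis).
- Patients: 30 at 1:1, so 15 per arm (Trial design and setting).
- Level: two-sided 0.05 for each efficacy test. This is an assumption.
- Correlation between scales: not given; assumed from 0 to 0.9.
- Success rule: not given; assumed to be that any one significant scale counts.

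**Independent scales.** P(at least one false positive) = 1 − (1 − 0.05)³ = 1 − 0.8574 = 14.3%. Ratio to 5%: 14.3/5 = 2.9.

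**Correlated scales.** Trials were simulated with no true effect, 15 per arm and a two-sample t-test on each of three equally correlated scales. Runs of 40,000 to 60,000 trials gave:

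| Between-scale correlation | At least one p < 0.05 | Multiple of 5% |
|---|---|---|
| 0 (exact) | 14.3% | 2.9 |
| 0.5 | 12.4% to 12.8% | 2.5 to 2.6 |
| 0.7 | 11.0% to 11.2% | 2.2 |
| 0.8 | 9.8% to 10.1% | 2.0 |
| 0.9 | 8.4% to 8.6% | 1.7 |

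The spread within a row is simulation error. With 60,000 trials and a rate near 10%, one standard error is √(0.10 × 0.90 / 60,000) = 0.12 percentage points. With 12 per arm (15 less 20% dropout) the results are nearly the same: 12.6% at correlation 0.5 and 8.6% at 0.9.

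Counting only false claims in favour of acupuncture, the nominal rate is 2.5%. The simulated rate is 4.3% at correlation 0.9, and 1 − (1 − 0.025)³ = 7.3% at 0. The ratios are about the same.

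**After the fix.** One named scale at one visit gives 5%. With three scales under Holm, the smallest p-value is compared with 0.05/3 = 0.0167, the next with 0.05/2 = 0.025 and the last with 0.05. Under independence and no effect, the chance of any rejection is 1 − (1 − 0.0167)³ = 4.9%.

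**The case against.** **It is a pilot.** There is no formal sample size, feasibility is a stated aim, and small size is an acknowledged limitation. Planning the next trial needs estimates and SDs, which error control does not improve. This stands as a reason to lower the severity. It does not remove the point, because the article also sets out to test efficacy and claims adequate power.

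**A full protocol or SAP may hold the detail.** Multiplicity rules, and which analysis set leads, are often placed there, so their absence from an article is not a fault in itself. The primary outcome is different: it belongs in the protocol, and this article has stated it as three unranked efficacy scales.

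**No any-one-scale rule is stated.** This is correct. Requiring all three scales would not inflate the error. The figures describe what the wording permits, not a known error rate. If the scales are close to interchangeable, the lower end of the range (about 8.5% to 10%) is the more plausible.

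Two stronger readings are tempting, and the documents do not support them.

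- *Three scales at two follow-ups make six primary tests.* Six separate tests would give 1 − 0.95⁶ = 26.5% if independent, and 15.2% with scale and time correlations both 0.8. But the later visit is only a collection point in the Primary outcome section. The between-group test is tied to end of treatment, and the later visit enters only through an optional repeated-measures ANOVA. Its role is left open; it is not planned as three more tests.
- *The paired t-tests create a quantifiable false efficacy claim.* Entry requires fatigue "whose symptom intensity is 4 or higher" on the NRS, so regression to the mean could produce improvement in both arms. If both arms change equally, the chance that only the acupuncture arm is significant is p(1 − p), where p is the paired-test power at n = 15. That is 0.438 × 0.562 = 24.6% at a change of 0.5 SD and 0.771 × 0.229 = 17.7% at 0.75 SD. It is 12.6% at 0.25 SD, 4.8% at 1.0 SD and 0.6% at 1.25 SD. The article gives no basis for choosing among these, and nowhere makes the paired tests a ground for claiming efficacy.

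**Conclusion.** The point holds for the single planned between-group comparison. Three scales are primary with no lead scale, no success rule and no error control, under an aim to test efficacy. The inflation of 1.7 to 2.9 times rests on three assumptions: each scale is tested at two-sided 0.05, any one significant scale is read as success, and between-scale correlations lie between 0.9 and 0. It excludes the later visit, the PP analysis and the choice between t-test and Wilcoxon, none of which is fixed well enough to count. Severity: should fix, since this is a pilot.

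**What to change.** Name one primary efficacy outcome. One option is the between-arm difference in change in fatigue NRS from baseline to end of treatment, in the ITT set; NRS is the scale that defines eligibility, but the choice is the sponsor's. BFI, FSS and the later follow-up then become secondary. The alternative is to keep all three scales primary and test them with Holm.

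Whichever is chosen:
- Give the end-of-treatment visit one label. It is week 4 under Trial design and setting and week 5 under Primary outcome.
- State whether the repeated-measures ANOVA is secondary.
- Report adverse events as the safety outcome.
- Say that the within-arm paired t-tests are descriptive and support no efficacy claim.

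The cost is a wording change in the protocol and registry entry, with the same patients and data. BFI and FSS lose the primary label, or, under Holm, the scales face stricter thresholds, starting at 0.0167 for the smallest p-value.

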### Secondary outcome

In addition to the primary outcome measurements, secondary outcomes will assess the comorbid symptoms of fatigue and feasibility variables of this study.

EuroQol-5-dimension 5 level (EQ-5D-5L) consists of 5 dimensions: mobility, self-care, usual activities, pain/discomfort, and anxiety/depression. It is used to assess overall quality of life by selecting the most appropriate statement among each of the five dimensions. The EQ-5D-5L will be administered at baseline, week 5, and week 13.

The Korean-validated version of the Insomnia Severity Index (ISI-K) assesses insomnia severity. It consists of 7 items using a 0–4 Likert scale. The sum of these scores becomes the total score, ranging from 0 to 28, and a cutoff score for discriminating insomnia patients is considered 15.5 (27). The ISI-K score will be assessed at baseline and at weeks 5 and 13.

Concomitant medications and changes in the treatment history will also be investigated. As all pharmacological or CAM interventions for any reasons will be not prohibited during the trial period, it will be recorded narratively at every visits.

The Was It Worth It (WIWI) questionnaire is to assess the feasibility of a clinical study by gathering participants’ opinion about their experiences in the study. It consists of 5 items, and subjects can choose one of 3 narrative answers. The results are evaluated qualitatively, not quantitatively (28). The WIWI will be measured at week 5.

For successful patient blinding, all subjects will be asked to guess whether they are allocated to the verum or sham acupuncture group at week 5. According to the correctness of the answer, it would be coded −1 or 1. If they answer that they do not know, it will be coded as 0.

To investigate the feasibility of the pilot RCT, the appropriateness of the study design, such as subject compliance to treatment and outcome sessions, selection rate during the study period, reasons for exclusion, and dropout rate, will be analyzed.

### Statistical analysis

Statistical analyses will be performed on both an intention-to-treat (ITT) basis and per-protocol (PP) population (95% confidence interval [CI]) using the SAS package program (Version 9.4; SAS Institute Inc., United States). Missing data will be replaced according to the last observation carried forward (LOCF) method. Baseline characteristics will be shown as mean ± standard deviation (SD) for continuous data and n (%) for categorical data. To analyze the baseline characteristics, we will conduct between-group comparisons at baseline using two-sample *t*-test or Wilcoxon rank sum test for continuous data and chi-squared test or Fisher’s exact test for categorical data with *p* < 0.05, as statistically significant, to determine whether the data are normally distributed.

For primary and secondary outcome measures, the mean difference from the baseline values to the end of treatment in each group will be compared using a two-sample *t*-test or Wilcoxon rank-sum test. If we needed to compare repeated measures, we would implement the repeated measures ANOVA. If any imbalances in baseline characteristics between groups were encountered, we will conduct analysis of covariance (ANCOVA) using these variables as covariates and the randomized group as a fixed factor. We might conduct subgroup analysis according to the baseline demographics, such as analysis on symptom duration over or under than 3-month period. In addition, to compare pre and post treatment assessment, we would use paired *t*-test, after evaluating the normality of the data. The safety and feasibility variables are descriptively presented with detailed explanations. Blinding assessment will be analyzed using Bang’s blinding index (29).

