### Trial design and setting

A two-arm, randomized, patient-assessor-blinded, sham-controlled trial will be conducted at the Kyung Hee University Korean Medicine Hospital in Seoul, Korea. This study was approved by the Institutional Review Board (IRB) of Kyung Hee University Korean Medicine Hospital (KOMCIRB 2023-04-006-001). Thirty participants will be recruited through subway advertisements and posters. Patient enrollment will begin in August 2023 and is expected to end in November 2023. Eligible and consenting patients will be randomly allocated to either the verum acupuncture or the sham acupuncture group at a ratio of 1:1. All subjects will receive twelve sessions of treatment for 4 weeks and will be assessed at baseline, week 4, and week 12. The trial design is summarized in Figure 1. Figure 2 outlines the SPIRIT schedule for enrollment, interventions, and assessments.

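### The primary fatigue scales are collected 8 weeks after treatment, but no between-group comparison is committed there; the conditional repeated measures ANOVA has no stated contrast and, over three visits, would not show persistence

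*Protocol article*

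**What the plan says.** Under Primary outcome, the protocol article lists the three fatigue scales (with adverse events) and states: "Outcome measures will be collected at baseline and at weeks 5 and 13". The abstract puts the last visit 8 weeks after treatment completion. Trial design and setting labels the visits differently ("will be assessed at baseline, week 4, and week 12"). I take these as the same two post-baseline visits and call them end of treatment and follow-up.

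The Statistical analysis section makes one firm between-group commitment for efficacy: "the mean difference from the baseline values to the end of treatment in each group will be compared", by two-sample t-test or Wilcoxon rank-sum test. The other methods it names do not commit to a follow-up comparison:

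- **Repeated measures ANOVA** is conditional: "If we needed to compare repeated measures, we would implement the repeated measures ANOVA". No criterion for need is given.
- **ANCOVA** applies only if a baseline imbalance is found, and names no time point.
- **The paired test** ("to compare pre and post treatment assessment, we would use paired" t-tests) is a within-arm, before-after comparison.

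Missing data are to be filled by last observation carried forward (LOCF).

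**The concern.** The Introduction reports that improvement in the uncontrolled case series was still present at 4-week follow-up. In this trial, the controlled check of durability is the difference between arms at the 8-week follow-up. As written, that difference need not be estimated, and whether it is compared at all is left to a later judgement that could be made with the data in hand.

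If the fallback is used, a standard repeated measures ANOVA without a planned contrast does not give the group difference at follow-up. The limitations paragraph of the Discussion says that the data will feed the sample size of the full-scale trial. For a trial with a durability endpoint, that needs a follow-up difference and an SD, and an omnibus F test supplies neither.

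**Working it through.** **Inputs from the documents.** 30 patients, 1:1, so 15 per arm. The 20% drop-out allowance leaves 30 × 0.8 = 24, or 12 per arm. There are three visits.

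**Assumptions, since the documents give no effect size, SD or correlation.** SD 1; effect d = 0.8; two-sided 5% level; no missing data; equal correlation ρ = 0.5 between visits, varied from 0.3 to 0.7; and one unequal pattern: 0.6 (baseline, end of treatment), 0.5 (baseline, follow-up), 0.8 (end of treatment, follow-up). The plan has no figure of its own to reproduce on this point.

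**Profiles of the group difference over the three visits.** Lasting (0, d, d); vanished (0, d, 0).

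**1. Group effect over three visits.** It estimates the mean of the profile.
- Lasting: (0 + d + d)/3 = 2d/3. Vanished: (0 + d + 0)/3 = d/3. Neither depends on SD or correlation.
- Standard error = √[(2/n)(1 + 2ρ)/3] = √[(2/15)(2/3)] = 0.298.
- Lasting effect: 0.533/0.298 = 1.79 on 28 df, power 41%.
- Vanished effect: rejects 14%.

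**2. Omnibus group-by-time test.** Noncentrality = (n/2) Σ(d_t − mean d)² / (1 − ρ).
- Lasting: Σ = d²(4/9 + 1/9 + 1/9) = (2/3)d².
- Vanished: Σ = d²(1/9 + 4/9 + 1/9) = (2/3)d², the same.
- Both give 7.5 × (2/3 × 0.64)/0.5 = 6.4 on 2 and 56 df, power 59%.

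**3. Baseline-adjusted contrast at follow-up (ANCOVA).**
- Standard error ≈ √[(2/n)(1 − ρ²)] = √[(2/15)(0.75)] = 0.316.
- Lasting: 0.8/0.316 = 2.53 on 27 df, power 68% by this formula and 67% by simulation, which also allows for chance baseline differences.
- Vanished: expected difference 0, rejects 5%.

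**Results, 15 per arm, d = 0.8 (20,000 simulated trials per case):**

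| Test | ρ = 0.5, lasting | ρ = 0.5, vanished | 0.6/0.5/0.8, lasting | 0.6/0.5/0.8, vanished |
|---|---|---|---|---|
| Group effect, three visits | 41% | 14% | 36–37% | 13% |
| Group-by-time, three visits | 59% | 59% | 67% | 79% |
| Follow-up ANCOVA | 67% | 5% | 66–68% | 5% |

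Under the unequal pattern the group-by-time test rejects more often when the effect has gone, and its type I error is about 6%.

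**Sensitivity.** For a lasting effect at ρ = 0.3/0.5/0.7, the closed forms give 49/41/35% for the group effect, 45/59/82% for group-by-time and 60/68/84% for follow-up ANCOVA. With 12 per arm and ρ = 0.5 they give 33%, 49% and 58%.

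**4. ANOVA on the two post-baseline changes only.** Its group-by-time term compares end of treatment with follow-up. It rejects 5% for a lasting effect, and for a vanished one 56% (ρ = 0.5) or about 91% (unequal pattern). This version does separate the two cases, but the plan does not state it.

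**The case against.** The case against has real substance.

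- **Detail for an analysis plan.** Time levels and visit contrasts are often left to a plan that is not shown, and repeated measures ANOVA does not preclude visit contrasts. That stands as to model detail. It does not answer the main point: the article itself fixes the end of the committed comparison and makes anything further conditional.
- **Follow-up as a primary time point.** A reader might infer this. The text lists collection times and names no primary time point, and EQ-5D-5L and ISI-K share the schedule. End of treatment can fairly be read as the lead comparison.
- **Repeated measures ANOVA cannot tell a lasting from a vanished effect.** This is too strong. Equal rejection holds for the three-visit omnibus test under equal correlations. Elsewhere the rates differ, and the two-change version separates the cases.
- **The ANOVA always has the least power.** It does not. At ρ = 0.3 its group effect has 49%, above the follow-up change-score test at about 43%, though below follow-up ANCOVA at every correlation tried.
- **A large power gain.** A baseline-adjusted mean of both post-treatment visits reaches 84% at ρ = 0.5. That too is a pooled effect, not the follow-up contrast, whose power is 67%.
- **This is a pilot.** No formal sample size was set, so power is secondary. I agree; the case rests on having an estimate at follow-up.

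**Conclusion.** The concern holds in a limited form. No between-group comparison of the primary fatigue scales at follow-up is committed, and the conditional fallback has no stated contrast. If it is run over all three visits, its group effect shrinks a lasting effect by one third, and a significant group-by-time result is not evidence that the effect lasted. The factors 2/3 and 1/3 do not depend on SD or correlation. The equality of the two group-by-time rejection rates needs equal correlations.

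The power figures rest on the assumed d, SD and correlations. A named follow-up contrast gains about 8 points over group-by-time at ρ = 0.5 (67% against 59%) and nothing under 0.6/0.5/0.8. Its main value is that it estimates d if the effect lasts and zero if it has gone. The documents do not support saying that every repeated measures ANOVA would fail here, or that the trial loses a large amount of power.

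**What to change.** In the Statistical analysis section, replace the conditional repeated measures ANOVA sentence with a commitment along these lines: for NRS, BFI and FSS, the baseline-adjusted group difference with 95% CI will be reported at end of treatment (lead comparison) and at the follow-up 8 weeks later (durability, supportive). Use either ANCOVA at each visit with the baseline score as covariate, or one mixed model for the two post-baseline visits with group-by-visit contrasts. ANCOVA per visit is enough for a pilot of this size.

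The LOCF sentence must change with it. Carrying end-of-treatment values into follow-up can make a vanished effect look lasting, and would feed filled-in values to a mixed model as if observed. Use observed data or the mixed model for the follow-up contrast, with LOCF at most as a sensitivity analysis.

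The cost is slightly more analysis work and one more reported contrast per scale. The data are already planned and the SAS version already named suffices. The follow-up interval will be wide: at ρ = 0.5 and 15 per arm, about ±2.05 × 0.316 = ±0.65 SD. It should therefore be presented as an estimate for planning the next trial.

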### Randomization and blinding

Randomization will be performed by an independent statistician using a computerized randomization with R package (R Version 4.3.1, Windows) with 1:1 allocation ratio. Prior to randomization, the study coordinator will ensure that each participant met the inclusion and exclusion criteria and informed consent is obtained. Random allocation will be conducted by an independent study coordinator, who will open the corresponding envelope in front of the participant.

The participants, outcome assessors, and statisticians will be blinded to the allocation, whereas practitioners will not. To evaluate the blinding, patients will assess their allocation guess and credibility rating immediately after the last treatment session.

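### Model choice depends on observed baseline imbalance and the outcome's own baseline is not a standing covariate, which costs precision and leaves conditional bias after a chance imbalance

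*Protocol article*

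**What the plan says.** The Statistical analysis section sets out three linked steps.

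1. Baseline characteristics are tested between arms at p < 0.05: "we will conduct between-group comparisons at baseline using two-sample *t*-test or Wilcoxon rank sum test for continuous data", with chi-squared or Fisher tests for categorical data.
2. For primary and secondary outcomes, "the mean difference from the baseline values to the end of treatment in each group will be compared using a two-sample" t-test or a Wilcoxon rank-sum test. No covariate is named.
3. ANCOVA is conditional: "If any imbalances in baseline characteristics between groups were encountered, we will conduct analysis of covariance (ANCOVA) using these variables as covariates", with randomised group as the fixed factor.

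The section does not define imbalance. The p < 0.05 baseline tests are the only criterion it offers. It also does not say whether a triggered ANCOVA replaces the test on change or accompanies it.

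On size, the Participants section says "Our study will recruit 30 patients, based on previous studies that recommended the minimum number of people necessary for preliminary research" and "A formal sample size calculation was not performed because this was designed as a pilot study". It allows for dropout ("considering a 20% drop-out") and requires an NRS of 4 or more at entry. Allocation is "with 1:1 allocation ratio", so 15 per arm.

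**The concern.** Under proper randomisation any baseline difference is due to chance, so a baseline p-value does not show which covariates predict the outcome. Using it to choose the model has two consequences. A variable that matters little can enter because it happened to differ. The variable most likely to matter, the baseline score of the same scale, stays out unless it is itself flagged. If only age is flagged, for example, age enters the ANCOVA and baseline fatigue does not.

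The default is also less efficient than ANCOVA. A change score fixes the coefficient of baseline at 1, whereas the regression of follow-up on baseline usually has a slope below 1. The estimate therefore carries avoidable noise, and when the arms differ at baseline by chance it is pushed in the opposite direction to that gap.

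This is a rule the protocol states, not a detail left to a later document. Although the trial is a pilot, Study objectives lists testing efficacy as part of the first aim, and the Discussion says the data will be used to calculate the sample size of the full-scale trial.

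**Working it through.** **Inputs from the protocol.** N = 30 at 1:1, so 15 per arm; 20% dropout leaves 24, or 12 per arm; baseline tests at p < 0.05 (taken as two-sided); NRS of 4 or more at entry. The sample size rests on no power formula, so there is no planned power to reproduce.

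**Assumed, because the protocol does not give them.** Baseline-outcome correlation (rho) 0.3 to 0.7; an illustrative effect of 0.8 SD; normal data; the t-test branch; imbalance read as p < 0.05; a triggered ANCOVA replaces the test on change.

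**Step 1. What the baseline test can flag.** The smallest flagged gap is t(0.975, 2n - 2) x sqrt(2/n).
- 15 per arm: 2.048 x 0.365 = 0.748 SD.
- 12 per arm: 2.074 x 0.408 = 0.847 SD.

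For any one variable at 15 per arm, a gap above 0.5 SD occurs in about 17% of trials. In about 12% it exceeds 0.5 SD and still passes the test.

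**Step 2. The outcome's own baseline.** The change score subtracts the whole gap, whereas regression supports subtracting slope x gap. The over-correction is (1 - slope) x gap. With equal SDs the slope equals rho, so for a 0.748 SD gap it is:
- rho 0.3: 0.7 x 0.748 = 0.52 SD
- rho 0.5: 0.5 x 0.748 = 0.37 SD
- rho 0.7: 0.3 x 0.748 = 0.22 SD

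Among simulated null trials with an unflagged gap above 0.5 SD, the change-score test rejects in 10.4%, 8.9% and 7.5% respectively. ANCOVA rejects in about 5%.

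**Step 3. Precision, scales without an entry cut (BFI, FSS, ISI-K).** Change-score variance is 2 x SD^2 x (1 - rho) and ANCOVA variance is SD^2 x (1 - rho^2), so the ratio is (1 + rho)/2. Estimating the slope multiplies it by (N - 3)/(N - 4) = 27/26.

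| rho | (1 + rho)/2 | x 27/26 | Power, plan | Power, ANCOVA |
|---|---|---|---|---|
| 0.3 | 0.65 | 0.68 | 44% | 59% |
| 0.5 | 0.75 | 0.78 | 57% | 67% |
| 0.7 | 0.85 | 0.88 | 78% | 83% |

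Power is simulated at 15 per arm, applying the plan's rule to the outcome's own baseline. Repeat runs differ by about one point in power and 0.01 in the variance ratio.

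**Step 4. Precision, NRS.** The entry cut shrinks the baseline SD but leaves the slope unchanged, so the equal-SD formula does not apply. Assume SD 2 and mean 5 or 6 before the cut, with baseline then limited to 4 to 10. The baseline SD falls to 0.66 or 0.72 of its uncut value. At an uncut rho of 0.5, in uncut SD units:
- change-score variance = (1 - 0.5)^2 x 0.66^2 + 0.75 = 0.86 (mean 5), or 0.88 with 0.72 (mean 6)
- ANCOVA variance = 0.75 x 27/26 = 0.78
- ratio = 0.91 or 0.89

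The correlation falls to 0.36 to 0.39 while the slope stays at 0.50. Over uncut rho 0.3 to 0.7 the simulated ratio is about 0.81 to 0.96, and the power gain runs from about 8 points down to about 2.

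**Step 5. Type I error.** Under the two-stage rule it is about 4 to 5% in every setting. ANCOVA gives about 5%.

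**The case against.** The strongest reply is that the plan remains valid. A change-score comparison is unbiased over randomisation and type I error is not inflated, so part of this is a preference between two legitimate estimators. That is right about validity. It does not answer the loss of precision or the bias that appears once a chance gap has occurred.

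A reader might infer that imbalances of up to 0.75 SD go uncorrected. The protocol does not support this for the outcome's own baseline, which the change score subtracts in full: that gap is over-corrected. It is fair only for other variables, such as age or symptom duration. Even there the 0.75 SD figure depends on reading imbalance as p < 0.05, which the text implies but does not state, and on all 30 patients being analysed.

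A reader might also infer that the NRS entry cut makes the loss worse by lowering the correlation. It does the reverse. Over-correction depends on the slope, which selection on baseline does not change, and the smaller baseline spread reduces what ANCOVA can gain. BFI and FSS have no cut of their own but also measure fatigue, so selection on NRS may restrict them indirectly and bring their gain below the table's figures.

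Finally, this is a pilot without a formal sample size, so no powered confirmatory test is lost. That limits the weight of the point. It does not remove it, since efficacy is a stated aim.

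**Conclusion.** The point holds as one of efficiency and prespecification, not of validity. The plan lets observed imbalance choose the model and does not guarantee that baseline fatigue is in it.

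Under the assumed correlations, always adjusting for baseline removes about 12% to 32% of the variance for scales without an entry cut, and about 4% to 19% for the NRS. For an illustrative 0.8 SD effect that is about 5 to 15 power points and 2 to 8 points respectively. The size rests on a correlation and an effect that the protocol does not give, on normal data, and on ANCOVA replacing the test on change when triggered. The rank-sum branch was not evaluated.

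The direction is less sensitive: with equal SDs, (1 + rho)/2 is below 1 for every correlation below 1, before the small cost of estimating the slope. A claim of inflated false-positive error overall would not be supported.

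**What to change.** For NRS, BFI, FSS, ISI-K and EQ-5D-5L, make the between-group analysis an ANCOVA of the end-of-treatment score (week 5 in the outcome sections) on randomised arm, with the baseline value of the same scale as covariate, whatever balance is observed. Drop baseline significance tests as the trigger and present baseline data descriptively. Name any further covariate in advance. Keep the t-test or rank-sum test on change as a sensitivity analysis.

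The cost is one degree of freedom and a change of wording. The baseline scores are already collected, so no patient, visit or measurement is added.
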